## 3.3 Study Design

The study will be conducted in the main PHCs of six suburbs in Southwest Harare. Each participating PHC will offer PITC routinely to 6-15 years olds over a two year period, a well as decentralised HIV care including ART initiation. Thus, children who test HIV-positive through PITC will be offered HIV care at the same PHC. At the end of two years of implementation of PITC, an anonymised HIV prevalence survey of 8-17 years olds from randomly selected dwellings in the suburbs served by the study PHCs will be conducted. The prevalence of *undiagnosed* HIV infection in the community following two years of PITC will provide an indication of the effectiveness of primary-care based routine HIV testing in providing high enough coverage of HIV diagnosis in this age-group (>80% of children diagnosed). The survey will also provide data on overall HIV prevalence by age in the considered age-group.

Children who test HIV-positive through PITC at the PHCs and reside in the study suburb where the clinic is located will be recruited into a trial of a VLW-delivered intervention to support to households of HIV-infected children aged 6-15 years. Stratified sampling will be used with randomisation of participants within clinics (1:1) to either a) primary care based HIV care or b) primary care-based HIV care plus treatment support provided by VLWs.

The intervention will be delivered over an eighteen month period, with formative work carried out to inform the design of the intervention. This will consist of qualitative interviews with care-givers of HIV-positive children attending for HIV care and health care providers (nurses, doctors, counsellors and pharmacists) at Harare Central Hospital as well as Community-based Organizations to understand the needs of households with HIV-infected children.

Children testing HIV positive at the PHCs including those recruited into the trial, will be recruited into a clinical cohort study. Data from routine clinic visit (including height, weight, clinical symptoms, incident clinical events and adherence) will be collected. In addition, detailed growth monitoring, lung function testing and a psychosocial assessment (i.e. schooling, guardianship, and disclosure) will be carried out at pre-defined intervals. The HIV care cohort will also provide a platform for immunological studies of slow-progression of HIV infection.

## 3.4 Study outcomes

### 3.4.1 PITC intervention

- Proportion of attendees who 1) accept HIV testing and 2) test HIV+ve following PITC
- Prevalence of undiagnosed HIV infection in the community two years post PITC implementation

### 3.4.2 Individual-randomised trial of household support

The unit of randomization will be an individual attending each clinic, and not households, however, the trial outcomes will be evaluated at the level of the clinic to cater for any clustering at clinic (suburb) level. The main differences between the two arms will be:

- Proportion on ART with treatment failure defined as an HIV-1 viral load >400copies/ml at 12 months after starting ART or death in the first year of ART
- Proportion who miss two or more *routine* appointments by the end of two years of follow-up

Other comparisons between arms will include:

1. all-cause mortality
2. numbers of and time to first hospital admission (defined as stay in hospital for ≥24 hours)
3. numbers of additional attendances (over and above routine follow-up) to PHC
4. proportion of children who have an average adherence rate <80% 12 months after starting ART
5. proportion of children who change to 2nd line ART as defined by National Guidelines (due to reasons not related to toxicity, side-effects or starting TB treatment)

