## 1.2 Aims

The objective of the study is to investigate whether a package of services at primary care level will adequately meet the needs of vertically HIV-infected children and adolescents, or alternatively whether further decentralisation to provide community-level HIV testing and/or treatment support is required.

Specific aims are:

1. To investigate the impact of treatment support provided by lay volunteers to households with one or more HIV-infected children aged 6-15 years on adherence and retention into HIV care.
2. To investigate the effectiveness of routine facility-based HIV testing and counselling in reducing rates of undiagnosed HIV infection among children aged 6-15 years in the community, over a relatively short period of time.
3. To assess the effect of ART on lung function and growth in HIV-infected children aged 6-15 years.

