**CLINICAL COHORT STUDY**

Obtain consent to participate; PITC for siblings and guardians

Cotrimoxazole prophylaxis for all & start ART when eligible according to

National Guidelines

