## 3.2 Objectives

The broad aim of this study to investigate whether a package of services at primary care level will adequately meet the needs of vertically HIV-infected children and adolescents, or alternatively whether further decentralisation to provide community-level HIV testing and/or treatment support is required.

The study has three main components:

1. To investigate whether routine facility-based HIV testing and counselling of children aged 6-15 years attending acute primary care services provides high coverage of timely diagnosis of HIV in the clinic catchment areas.
2. To conduct a randomised control trial comparing a) optimised primary HIV care services alone with b) optimised primary HIV care services plus treatment support provided by VLWs to households with one or more HIV-infected older children.
3. To add serial lung function and anthropometry to the routine follow-up schedule of newly diagnosed children retained in HIV care, in order to investigate the safety of current deferred-start ART guidelines in this age-group (WHO stage 3/4 disease or CD4 count < 350cells/µl).

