# METHODS AND PROCEDURES

## 5.1 Routine PHC based PITC

All children aged 6-15 years attending for acute care at primary health care clinics (PHC) in seven of the 10 high density suburbs of southwest Harare (Highfield, Glen View, Budiriro, Kuwadzana, Mufakose, Dzivarasekwa, Glen Norah) will be offered routine provider-initiated testing and counselling (PITC) during a two year period. Training on HIV testing and counselling of children will be provided through PSI.

A research assistant will be based at the clinic and will identify children eligible for PITC and refer them for HIV testing to PHC counsellors/nurses. After clinic registration, the standard approach to PITC developed by the Ministry of Health and Child Welfare will be used. All eligible clinic attendees will be given brief standard pre-test counselling followed by an offer of HIV testing and post-test counselling. Guardian consent will be required for children to undergo HIV testing. Children attending without a guardian will be given information about HIV testing and encouraged to re-attend with a guardian for HIV testing.

HIV test results will be given to the child and their guardian at the same clinic visit, with age-appropriate explanation of HIV test results given to the child. Children who test positive will be offered enrolment into HIV care at the PHC where they test. Biological parents, guardians and natural siblings of children who test HIV-positive will be offered HIV testing. Attendees who decline HIV testing will be assessed for their presenting health problem by the clinic nurse. PITC outcome will be recorded as accepted/ absent guardian/ testing for subject declined /testing for guardian declined.

HIV testing kits will be provided by the National HIV Program. The research assistants will ensure that a supply of testing kits is always available at the PHCs. Diagnostic HIV testing will be carried out using two HIV rapid tests (Abbott Determine™ and SD Bioline™) run in parallel. Discordant specimens will be resolved using a third rapid HIV test (INSTI™).

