# HOUSEHOLD-LEVEL VLW SUPPORT

Community-based adherence support will be provided to families enrolled in the ZENITH trial by Voluntary Lay Workers (VLW) who will be recruited and trained to offer psychosocial counselling, practical advice, and links to appropriate referrals. The exact structure of the intervention, including guidelines and protocols specifying the nature and frequency of activities provided by VLWs, will be determined following the formative research described in Section 5.4, which will identify locally important facilitators and barriers experienced by the primary caregivers of HIV+ children. However, the LHW programme will centre around a series of home visits to (1) assess each enrolled family’s circumstances and needs; (2) identify feasible measures that caregivers might put in place to maximise engagement with care; (3) offer both general support and tailored assistance, following standardised guidelines; and (4) refer families to locally available organisations offering additional support services. Finally, LHW will serve as a link to the HIV treatment services by reminding caregivers of scheduled appointments, and following-up with clinic staff to check families’ attendance and identify emerging concerns that could lead to attrition from care.

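### Support delivered to the household is allocated child by child, with no rule for siblings, so some control children would share a home with the intervention and the effect would be biased toward zero

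*Protocol*

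**What the plan says.** On allocation, Section 3.4.2 is explicit: "The unit of randomization will be an individual attending each clinic, and not households". Section 5.3.1 stratifies by clinic, allocates 1:1 within each clinic, and issues study numbers consecutively with the arm already attached. No section says what happens when a second child from an enrolled household joins. The only clustering mentioned is by clinic: "the trial outcomes will be evaluated at the level of the clinic to cater for any clustering at clinic (suburb) level".

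On the intervention, the first aim in Section 1.2 is to study "treatment support provided by lay volunteers to households with one or more HIV-infected children aged 6-15 years", and Section 3.2 likewise describes "treatment support provided by VLWs to households with one or more HIV-infected older children". Section 6 opens with "Community-based adherence support will be provided to families enrolled in the ZENITH trial". It goes on to describe home visits that assess the family's needs, help caregivers plan, remind them of appointments and check attendance with the clinic.

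On siblings, Section 5.1 says "Biological parents, guardians and natural siblings of children who test HIV-positive will be offered HIV testing", and Figure 1.1 has "Obtain consent to participate; PITC for siblings and guardians". Under Section 6.1, lay workers are trained to encourage testing of other family members. The criteria in Section 4.5 (age, positive PITC result, residence, care at the PHC, consent) set no limit of one child per household.

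**The concern.** The intervention works through the caregiver. A lay worker who reminds a caregiver of one child's appointment, or helps her organise one child's treatment, is likely to affect the other infected child she looks after. The protocol actively looks for that second child and, as written, allocates the child independently. When two siblings fall in opposite arms, the control sibling lives with the support that the trial is meant to withhold.

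Both main outcomes are exposed. Missed appointments is the outcome closest to caregiver reminders, and treatment failure depends on adherence that the caregiver supports. Contaminated controls pull both differences toward zero. Analysis cannot fully undo this, and evaluating outcomes by clinic does not touch it, because the leakage happens inside the home.

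**Working it through.** **1. Reproducing the plan's power.** Inputs from Section 11.2.1: 175 per arm, 10% loss, 30% of controls missing two or more appointments, 45% relative reduction. The significance level is not stated; I assume two-sided 5%.

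- Evaluable per arm: 175 × 0.9 = 157.5.
- Intervention rate: 0.30 × (1 − 0.45) = 0.165.
- Two-proportion normal approximation, no continuity correction: power 81.3% (stated: 80%).
- The plan's other two figures are reproduced with a continuity correction: 40% v 24% gives 83.6% (stated 83%), and 50% v 30% with 123 per arm gives 87.2% (stated 87%).

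No single variant fits all three: with the correction, the first scenario gives 77.4%. All variants assume independent children and no contamination.

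**2. How often pairs split.** Under 1:1 individual allocation a sibling pair is split with probability of about 0.5. With 10 pairs, about 5 are split, and the chance of at least one is 1 − 0.5¹⁰ = 99.9%.

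**3. Dilution.** Let s be the share of trial children with a co-enrolled sibling (pairs assumed) and t the fraction of the effect that reaches an exposed control child. The exposed share of controls is s/2, so

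control rate = 0.30 − (s/2) × t × 0.135.

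The documents give neither s nor t; both are assumed over a range. Power against 16.5% with 157.5 per arm:

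| s | Control rate, t = 1 | Reduction seen | Power, t = 1 | Power, t = 0.5 |
|---|---|---|---|---|
| 0 | 30.0% | 45.0% | 81.3% | 81.3% |
| 5% | 29.7% | 44.4% | 79.5% | 80.4% |
| 10% | 29.3% | 43.7% | 77.5% | 79.5% |
| 20% | 28.7% | 42.4% | 73.4% | 77.5% |
| 30% | 28.0% | 41.0% | 68.9% | 75.5% |

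For treatment failure (50% v 30%, 175 × 0.7 = 122.5 per arm, uncorrected, t = 1), power is 89.6% at s = 0, then 88.1%, 86.5%, 82.8% and 78.4%.

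**4. Power if siblings share an arm.** Contamination between co-enrolled siblings disappears, and the design effect for pairs is 1 + s × ICC. Power for 30% v 16.5% with 157.5/(1 + s × ICC) per arm:

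| ICC | s = 10% | s = 20% | s = 30% |
|---|---|---|---|
| 0.3 | 80.1% | 79.0% | 77.8% |
| 0.5 | 79.3% | 77.4% | 75.6% |
| 1.0 | 77.4% | 73.8% | 70.3% |

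The ICC 0.5 row nearly matches the half-transfer column in step 3, and the ICC 1.0 row is close to the full-transfer column.

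**5. Standard errors under each rule.** I simulated the null with 316 children, a 30% event rate, 20-30% of children in pairs, within-pair correlation 0.3-0.7 and an unadjusted two-proportion test. Type I error was 4.7-5.3% under individual allocation and 5.9-7.5% when siblings share an arm. Under individual allocation, same-arm pairs add variance to the difference and split pairs remove it, and the two roughly cancel.

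**The case against.** **Few children may be affected.** Both siblings must be infected, aged 6-15, newly diagnosed and not in care, resident in the clinic's suburb, and consenting. Sections 2.1 and 11.1 put survival of infected infants to 10 years at 28%, so two such siblings in one home may be uncommon. At s = 5% the loss is one to two power points. This stands: the size is unknown and may be small.

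**Full transfer is a ceiling.** Some visit content, such as disclosure work and the visits repeated at ART start, is organised around the enrolled child. This stands too, and is why the half-transfer column is shown.

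**The text is silent rather than explicit.** No sentence says that siblings are randomised separately. Section 5.1 frames PITC around acute attenders, and only Figure 1.1 applies the PITC label to siblings. The trial SOPs are appendices that are not shown and might contain a household rule. That is fair, but Sections 3.4.2 and 5.3.1 fix the allocation unit, reject the household by name, and leave no room for such a rule as written.

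**Stronger readings to avoid.** A reader might infer that the current plan gives wrong standard errors because siblings are correlated. It does not: under individual allocation the test keeps close to its nominal level (step 5). How household correlation is analysed could also properly be left to an SAP. A reader might also infer that allocating siblings together recovers power. That follows only if full transfer is set against a low ICC; under matched assumptions the gain is about nil.

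**Conclusion.** The point holds as a matter of bias. The protocol allocates individually an intervention delivered to the household, seeks out siblings, admits them, and has no rule for the second child. About half of co-enrolled pairs would be split, and the estimated effect on both main outcomes would be pulled toward zero.

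The size rests on two quantities that the documents do not give. With s of 5-30%, the 45% reduction would be seen as 44.4-41.0% under full transfer. Power would be 79.5-68.9% under full transfer and 80.4-75.5% under half transfer, against 81.3% with no contamination. The lowest figure combines the largest assumed sibling share with the upper bound on transfer, so it should not be read as the expected loss. The plan's sample-size arithmetic is not wrong on its own inputs. This is a cheap improvement that should be made, not a flaw that invalidates the trial.

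**What to change.** In Section 5.3.1, randomise the first enrolled child of a household and assign any later-enrolled child of that household to the same arm. Record a household identifier at registration so that the rule can be applied; household structure is already collected at the initial assessment (Section 7.2). Amend the sentence on the unit of randomisation in Section 3.4.2 to agree.

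Because this rule creates household clustering within arms, the main analysis should use household-robust standard errors. Without them the rule would inflate type I error (step 5).

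The cost is one allocation rule, one data field, a small loss of effective sample size (design effect 1.03-1.09 at ICC 0.3 and 1.05-1.15 at ICC 0.5, for s of 10-30%) and possibly slight imbalance between arms. Section 11.2.1 should then restate power with the assumed sibling share and ICC.

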## 5.3 Randomisation and investigator blinding

Eligible participants who reside in the study suburb where the PHC is located will be randomly allocated to either standard HIV care or to standard care + the support intervention (1:1 in each clinic). If the child resides outside Harare, he/she will be offered standard clinic care but will be excluded from the trial and the cohort study. All children aged 6-15 years registering for HIV care at the clinic and resident in Harare will be invited to participate in the cohort study, even if they refuse participation in the trial. The PI will be blinded to the information on the trial arm each participant is allocated to until the end of the trial follow-up.

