**5.3.1 Randomisation Procedure**

Randomisation will use proportional stratified random sampling using computer generated pseudo –random numbers. The size of each strata will be proportionate to the population size of children aged 6-15 years who are serviced by the clinic (based on Census 2002 data) and are expected to be HIV positive (based on extrapolations from previous surveys in the same study suburbs)

- Stratification will be according to the recruitment clinic (6 clinics)
- The sampling fraction will be 0.175 to ensure that each clinic is allocated study numbers proportional to the expected population of children aged between 6-15 years who test HIV positive (sample which is proportional to size)
- Random allocation to either standard HIV care or to standard care + the support intervention of 1:1 at each clinic will be done, thereby each study number allocated to the clinic will be randomly allocated to either standard HIV care or to standard care + the support intervention
- As the children are recruited into the study, a study number will be allocated consecutively and the appropriate study arm linked to the number.

In the event that the child refuses to participate in the trial and/or is recruited in the cohort only a different study number will be allocated.

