## 11.2 Sample size estimates

### 11.2.1 Individual-randomised trial

A sample of 175 children with newly diagnosed HIV per arm provides 80% power to detect a 45% reduction in proportion of children who miss ≥2 routine appointments in the follow up period in the intervention arm relative to the standard of care arm, given the most likely scenario of 30% missing in the control arm 4, 86, and allow 10% loss to follow-up, assuming a baseline HIV prevalence of 1.8%. The study also has 83% power to detect a 40% difference in proportions who miss ≥2 appointments, assuming that rates in the unexposed arm is 40%.

Studies have shown virological failure rates of 30-70% in older children. 1, 87-88 Assuming that at least 70% of the 175 children per arm with newly diagnosed HIV start ART, we expect 123 children per arm to be on ART. If the treatment failure/death rate among controls is 50%, the study will have 87% power to detect a 40% reduction in this rate. Given that our retention rate into the trial is better than expected, 350 participants will therefore provide adequate power to detect the difference in retention in care between the trial arms, even with the lower sample size.

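### Section 3.4.2 evaluates outcomes at clinic level although clinic is a randomisation stratum; taken literally, this does not deliver the power in 11.2.1

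*Protocol*

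**What the plan says.** Protocol 3.4.2 sets the unit of randomisation: "The unit of randomization will be an individual attending each clinic, and not households". The same sentence then continues, after a contrasting conjunction: "the trial outcomes will be evaluated at the level of the clinic to cater for any clustering at clinic (suburb) level".

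The design sections treat clinic as a stratum. Section 3.3: "Stratified sampling will be used with randomisation of participants within clinics (1:1"). Section 5.3 says that eligible children "will be randomly allocated to either standard HIV care or to standard care + the support intervention (1:1 in each clinic"). Section 5.3.1: "Stratification will be according to the recruitment clinic (6 clinics").

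The sample size in 11.2.1 counts children: "A sample of 175 children with newly diagnosed HIV per arm provides 80% power to detect a 45% reduction". The treatment-failure calculation uses 123 children per arm. The section mentions no design effect, no between-clinic variance and no clinic-level unit. Section 9.2.2 likewise derives the missed-appointment endpoint as a proportion of participants in each arm.

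**The concern.** Clinic-level evaluation is the usual remedy when whole clinics are randomised. Here they are not. Every clinic contributes children to both arms, so a clinic with generally worse attendance raises the rate in both arms, and that difference drops out of a within-clinic comparison. Clinic differences of this kind call for stratification or adjustment. They do not call for replacing some 350 children by a handful of clinic summaries.

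The stated level of evaluation therefore fits neither the randomisation nor the sample-size calculation. An analyst who follows 3.4.2 to the letter loses power on both main outcomes. One who analyses children individually, as 11.2.1 implies, departs from the wording of 3.4.2.

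**Working it through.** **Inputs**
- Missed appointments (11.2.1): 175 per arm with 10% loss, so 175 × 0.9 = 157.5, taken as 158. Control 30% with a 45% reduction gives 0.30 × 0.55 = 16.5%. In the second scenario, control 40% with a 40% reduction gives 0.40 × 0.60 = 24%.
- Treatment failure or death (11.2.1): 123 per arm; control 50% with a 40% reduction gives 30%. The section takes no further loss from the 123, and none is taken here.
- Clinic sizes (Table 5.1, last column): 32, 37, 64, 49, 78, 47, 43, which add to 350.
- Number of clinics *k*: 6 in 5.3.1, but 7 in Table 5.1 and in 5.1 ("in seven of the 10 high density suburbs of southwest Harare"). Both are run.
- Significance level: not stated; two-sided 5% is assumed.

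**Step 1: reproduce the stated power at individual level**

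Power = Φ[(d − 1.96·SE0)/SE1], where d = p1 − p2, SE0 = √(2·p̄(1 − p̄)/n) and SE1 = √([p1(1 − p1) + p2(1 − p2)]/n). The continuity-corrected form uses d − 1/n in place of d.

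For 30% vs 16.5% at n = 158: SE0 = 0.0475, SE1 = 0.0469, and (0.135 − 1.96 × 0.0475)/0.0469 ≈ 0.89, which gives 81%.

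| Scenario | n per arm | Stated | Uncorrected | Continuity-corrected |
|---|---|---|---|---|
| 30% vs 16.5% | 158 | 80% | 81.4% | 77.5% |
| 40% vs 24% | 158 | 83% | 86.5% | 83.7% |
| 50% vs 30% | 123 | 87% | 89.8% | 87.2% |

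The stated figures are reproduced by one formula or the other, and both treat children as independent individuals.

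**Step 2: clinic as the unit, equal-sized clinics**

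A paired t-test on *k* within-clinic risk differences has k − 1 degrees of freedom and noncentrality d/SE1 if the effect is the same everywhere. For 30% vs 16.5% the noncentrality is 0.135/0.0469 = 2.88. The critical value is 2.57 for k = 6 and 2.45 for k = 7, against 1.96 for the individual-level test. Power is 64% (k = 6) or 67% (k = 7). The other scenarios give 70% or 73%, and 74% or 78%.

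**Step 3: clinic sizes in proportion to Table 5.1 (simulation)**

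The comparator is a Cochran-Mantel-Haenszel test on children, stratified by clinic. The six-clinic column omits PHC1; omitting PHC7 instead gives 60%, 66% and 71%.

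| Scenario | Stated | Paired t, 6 clinics | Paired t, 7 clinics | Individual-level, stratified |
|---|---|---|---|---|
| 30% vs 16.5% | 80% | 61% | 64% | 81–82% |
| 40% vs 24% | 83% | 67% | 70% | 86–87% |
| 50% vs 30% | 87% | 72% | 74% | 89–90% |

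**Step 4: sensitivity, 30% vs 16.5%**
- Weighting clinics by size adds about 3 points: 63% with 6 clinics, 67% with 7.
- Ignoring the pairing and testing 12–14 clinic-by-arm proportions gives 74–75% if clinics do not differ at all, and 48–52% if baseline rates vary between clinics with an assumed SD of 0.075.
- If the effect itself varies between clinics, equal-size paired power falls to 57–61% (assumed SD 0.05 on the risk-difference scale) or 42–47% (SD 0.10).
- Baseline clinic variation (assumed SD 0.3 on the logit scale) leaves the stratified individual-level test at about 81%.

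**The case against.** **The sentence may mean only adjustment for clinic.** This is the strongest reply. Section 3.4.2 names no test, summary statistic or number of units. It goes on to list differences between arms as proportions of children, and 9.2.2 computes proportions of participants per arm. On that reading the stated power holds. The reply stands as a limit on the finding: the power loss depends on the literal reading. It does not rescue the wording, which sets clinic-level evaluation against individual randomisation.

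**The analysis plan will settle the model.** It may, and it is not shown. The model detail is not the point here. The sentence already fixes a level of evaluation that conflicts with the design.

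**The shortfall depends on the choice of test.** Partly. A reader might infer that the protocol gives the smallest clinic the same weight as the largest. It does not; it states no weights, and equal weighting belongs to the test used for illustration. Size-weighting still leaves most of the gap.

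**Clinic clustering is not irrelevant.** Agreed. Only baseline differences between clinics drop out. Lay workers are recruited locally and linked to the local clinic (section 6), so the effect could vary by clinic. With zero average effect and an assumed between-clinic effect SD of 0.05 or 0.10, the stratified individual-level test rejects in about 7% or 12–13% of simulated trials, while the paired clinic-level test stays near 5%. Whether to infer to these clinics or to a wider set is a design judgement.

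**Conclusion.** The level of evaluation stated in 3.4.2 does not match the randomisation in 3.3, 5.3 and 5.3.1 or the power basis in 11.2.1. On the literal reading, power falls short of the stated figure by about 16–19 points for 30% vs 16.5%, 13–16 points for 40% vs 24%, and 13–15 points for 50% vs 30%. This assumes a two-sided 5% level, the clinic proportions of Table 5.1 and no variation in effect between clinics; such variation would lower clinic-level power further. On the adjustment reading there is no loss and the fault is one of wording.

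Two stronger inferences are not supported. One is that the trial is too small: 350 children give roughly the stated power under an individual-level analysis. The other is that treatment-failure power is lower still because 10% loss should be taken from the 123 per arm: 11.2.1 does not apply that loss to this outcome. The conflict between six and seven clinics is a separate matter and does not change the conclusion.

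**What to change.** Replace the clinic-level clause in 3.4.2 with wording such as: outcomes will be compared between arms at the level of the individual child, stratified by or adjusted for recruitment clinic, using a Mantel-Haenszel risk ratio or a binary regression with clinic as a fixed effect; clinic-level results will be shown descriptively.

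The cost is one sentence, with no added participants or data. The small downside is that the estimate then refers to these clinics, and its confidence interval does not reflect variation in effect between them. A clinic-by-arm summary table would let readers see any such variation.
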